### 1.6. Objectives and Hypotheses

The primary objective is to evaluate the attitudes of Romanian adults recruited online—acceptability, trust, risk perception, and responsibility attribution—toward four progressive scenarios of AI implementation in facial reconstructive surgery. The secondary objectives are (i) to analyze the moderating effect of AI familiarity on acceptability across autonomy levels; (ii) to investigate how responsibility attribution (surgeon, hospital, AI developer, unavoidable medical uncertainty) varies across scenarios; (iii) to explore the moral–legal distinction in responsibility attribution; (iv) to identify the preferred model of AI implementation in facial reconstructive surgery; and (v) to quantify the influence of presentation sequence on all primary outcomes and to estimate the autonomy effect adjusted for serial position.

Four hypotheses will be tested. H1. Acceptability and trust decrease significantly as the level of AI autonomy in the surgical decision increases. H2. Perceived risk increases as human control over the decision process decreases. H3. Responsibility attribution shifts progressively from the surgeon toward the AI developer as algorithmic autonomy increases. H4. Prior familiarity with AI moderates the relationship between implementation scenario and acceptability, such that participants familiar with AI show a smaller decline in acceptability for high-autonomy scenarios; H4 is treated as partially exploratory, given the power constraints described in Section 2.5. H1–H3 fix the expected direction but not the functional form: each is tested by an omnibus effect of autonomy level followed by the full set of orthogonal polynomial contrasts, so that threshold-like or otherwise non-monotonic patterns are detected rather than forced into a linear trajectory (Section 2.9.1). A design-validation hypothesis is tested alongside them, namely that responses do not depend on the sequence in which the scenarios were presented; it is evaluated as the scenario × sequence interaction, and a non-null result is treated as evidence of order dependence to be reported and adjusted for, not as a substantive finding about autonomy.

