
#### 2.9.2. Secondary and Exploratory Analyses

(i) Moderation (H4): the scenario × AI familiarity (B1, centered) interaction, via repeated-measures ANCOVA or a linear mixed model with random intercepts per participant, the recommended framework for vignette data [62]; presentation sequence is retained as a between-subjects factor here, as in every repeated-measures model in this protocol. (ii) Person-level multiple regression: mean acceptability across scenarios predicted by AI familiarity, general AI attitudes, and demographics (reporting *B*, *SE*, β, 95% CI, R^2^, VIF). (iii) Responsibility migration (H3): a 4 × 4 mixed ANOVA (scenario × actor, RES1–RES4, both within-subjects; presentation sequence between-subjects) with Greenhouse–Geisser correction; the scenario × actor interaction is the direct test of H3. Because H3 is confirmatory, it receives the same order controls as H1 and H2: the sequence terms are inspected first, and the migration estimate is repeated in a linear mixed model containing an additive serial-position term. (iv) Responsibility concentration: a normalized Herfindahl–Hirschman index computed per scenario from the relative weights of the three responsible actors (surgeon, hospital, AI developer; RES4—unavoidable medical uncertainty—is not a responsible actor and is analyzed separately), compared across scenarios by mixed repeated-measures ANOVA with sequence as a between-subjects factor; low values index diffusion of responsibility across actors, operationalizing the “problem of many hands” described in the responsibility literature [44,45]. (v) RES5 (moral duty) and RES6 (outcome-independent accountability): mixed repeated-measures ANOVAs across scenarios with sequence as a between-subjects factor, Holm-corrected within the family. (vi) Global preference (P1): a goodness-of-fit chi-square with standardized residuals over six analysis categories on 5 degrees of freedom. The six categories are the four scenarios, “I would prefer AI not to be involved in any way,” and a combined “no clear preference” category; the last pools the item’s two undecided options (“I have no preference” and “I cannot decide”), which are combined a priori because neither expresses a preference between scenarios and each is expected to be sparse. Consistency between stated preference and each participant’s maximum-acceptability scenario is reported descriptively. (vii) Exploratory: P4a and P4b (the surgeon’s permanent legal and, separately, moral responsibility) analyzed descriptively, compared with each other by a dependent-samples test on the within-person difference, and correlated with RES5/RES6; free-text concerns (P2) summarized by brief thematic analysis. (viii) Sensitivity analyses: primary analyses repeated (a) excluding participants with a single attention-check failure (who are retained under the primary rule) and (b) excluding participants with any comprehension failure, to demonstrate that conclusions do not depend on the cleaning criteria [69]. (ix) Order effects: descriptive profiles by sequence, the scenario × sequence interaction with its effect size and 95% confidence interval, and sequence-specific manipulation-check profiles. (x) Response-pattern typology (exploratory): where the random-slope test of Section 2.9.1 indicates heterogeneity, individual acceptability trajectories across autonomy levels are classified by latent-class growth analysis, with class enumeration by BIC and entropy and a minimum class size of 5% fixed in advance, and class membership described against AI familiarity, healthcare-system trust, and demographics; no inferential claim is attached to this analysis. (xi) Healthcare-system trust (B6) enters the person-level regression of (ii) as a covariate and is examined as an exploratory moderator of the autonomy effect, alongside healthcare contact frequency (B5) and prior surgical experience (B4, B4a). (xii) Subgroup analyses, all of which are secondary or exploratory, are governed by a minimum-cell rule fixed in advance: inferential tests within a subgroup are reported only where that subgroup contains at least 50 valid participants, the size at which a within-subject difference in *dz* = 0.40 is detectable at power 0.80; subgroups of 30–49 are reported descriptively with 95% confidence intervals and labeled as underpowered; subgroups below 30 are pooled into a residual category or not reported. A difference between subgroups is never inferred from a significant effect in one and a non-significant effect in another; only the formal interaction term, with its own confidence interval, supports such a claim. The set of moderators is fixed a priori, in the pre-registration, to seven: AI familiarity (B1), healthcare-system trust (B6), healthcare contact frequency (B5), prior surgical experience (B4/B4a), education (D3), age (D2), and field of activity (D4). Results are reported for all seven irrespective of significance, and no further moderator is added after the data are seen. (xiii) Missing data: because all closed items are mandatory, missingness in the dependent variables is structurally impossible within a submitted questionnaire. Two other forms of missingness remain. The first is unit-level, from questionnaires abandoned before submission. The platform is configured not to store partial submissions, so responses from abandoned questionnaires are neither retained nor analyzed (Section 2.10 and Appendix A.1). Attrition is therefore characterized from the platform’s page-level counters—how many participants reached each page—rather than from partial response data, and is reported as drop-out by serial position in the participant-flow diagram. Analyses are accordingly restricted to complete cases, that is, participants with all four scenario blocks, and no imputation is performed: with no partial records retained, there are no incomplete cases to impute. The second is item-level, on the background and demographic items that offer a “prefer not to answer” option or, in the case of B4 and B4a, are not displayed where the explicit health-data consent is declined; these are treated as a distinct category descriptively and as missing in inferential models, with a sensitivity analysis retaining the category in the person-level regression. Because complete-case analysis is not neutral when attrition is differential, drop-out is compared across the four presentation sequences, and any imbalance is reported and carried into the interpretation of the order analyses. All tests are two-tailed at α = 0.05, with exact *p*-values, effect sizes, and 95% confidence intervals reported for all tests, including non-significant ones. On closed 1–7 scales, no distribution-based outlier removal is applied.

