## Figures and Tables

**Figure 1 healthcare-14-03030-f001:**
[figure not shown]
Achieved power of the primary repeated-measures ANOVA (four within-subject levels, α = 0.05) as a function of the number of valid responses, for small (*f* = 0.10, at ρ = 0.50 and ρ = 0.30) and medium (*f* = 0.25) effects. Dotted reference lines mark power = 0.80 and the two pre-specified thresholds (*N* = 140, minimum analyzable; *N* = 300, recruitment target). Curves are computed analytically from the noncentral *F* distribution. Entering presentation sequence as a between-subjects factor consumes three degrees of freedom from the error term and leaves these curves unchanged to within rounding.

**Table 1 healthcare-14-03030-t001:** The four experimental scenarios. The labels A–D denote autonomy level, not position in the sequence; scenarios are administered in one of four counterbalanced sequences (see Section 2.1).

Scenario	Label	Role of the AI System	Role of the Surgeon
A	Imaging assistance	Analyzes the CT scan and highlights anatomical structures (e.g., bone density, tissue layers)	Independently interprets the AI output and makes all decisions on the surgical plan
B	Decision support	Proposes three possible surgical plans, each with different advantages and disadvantages	Reviews all options, selects the most suitable plan, and may adjust it
C	Outcome simulation	Generates 3D simulations of postoperative facial appearance for each surgical option	Reviews the simulations, discusses them with the patient, and decides the final plan
D	Autonomous planning	Generates a complete, optimized surgical plan	Reviews the plan before surgery; modifications to the AI proposal are rare

**Table 2 healthcare-14-03030-t002:** Minimum detectable effects (power = 0.80, α = 0.05).

Test	Parameters	Minimum Detectable Effect
RM-ANOVA, 4 within-subject levels	*N* = 24, ρ = 0.50	*f* = 0.25 (medium)
RM-ANOVA, 4 within-subject levels	*N* = 140, ρ = 0.50	*f* = 0.10 (small)
RM-ANOVA, 4 within-subject levels	*N* = 300, ρ = 0.50	*f* = 0.07
Dependent pairwise comparison	*N* = 300, α = 0.05	*dz* = 0.16
Dependent pairwise comparison	*N* = 300, α = 0.05/6	*dz* = 0.20
Scenario × familiarity interaction (*df* = 3)	*N* = 300, α = 0.05	*f*^2^ = 0.037
Goodness-of-fit chi-square, preference (*df* = 5)	*N* = 300, α = 0.05	*w* = 0.21
Autonomy main effect, sequence as between-subjects factor (*df* = 3)	*N* = 300, ρ = 0.50	*f* = 0.07

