Scenario × sequence interaction—order test (*df* = 9)	*N* = 300, ρ = 0.50	*f* = 0.08
Scenario × sequence interaction—order test (*df* = 9)	*N* = 300, ρ = 0.30	*f* = 0.10
Pilot order bound, ascending vs. descending arm (*df* = 3)	*N* = 50, ρ = 0.50	*f* = 0.17
Dependent comparison within a demographic subgroup	*n* = 50, α = 0.05	*dz* = 0.40

Abbreviations: RM-ANOVA, repeated-measures analysis of variance; *N*, number of valid participants; *n*, number of participants per pilot arm or subgroup; ρ, correlation between repeated measurements; α, significance threshold; *df*, degrees of freedom; f and *f*^2^, Cohen’s effect-size indices for *F* tests; *dz*, Cohen’s effect size for dependent-samples comparisons; *w*, effect size for the goodness-of-fit chi-square test.

**Table 3 healthcare-14-03030-t003:** Projected recruitment funnel.

Stage	Assumed Pass Rate	Estimated Number
Link accesses	—	≈545
Begin questionnaire (consent given)	85% of accesses	≈463
Eligible after screening (items S1, S2)	96% of starters	≈445
Completed (submitted) questionnaires	75% of eligible	≈334
Valid after quality exclusions (ATT, CC, invariant, duplicates)	90% of submitted	≈300

Abbreviations: S1 and S2, the two screening items of the instrument (Appendix A.1); ATT1 and ATT2, attention checks; CC_A–CC_D, comprehension checks.

**Table 4 healthcare-14-03030-t004:** Measurement structure of the instrument.

Construct/Variable	Items	Scale	Role in Analysis
Acceptability	ACC1–ACC3 (mean), per scenario (×4)	Likert 1–7	Primary DV (H1), within-subjects
Trust	TRU1–TRU3 (mean), per scenario (×4)	Likert 1–7	Primary DV (H1), within-subjects
Perceived risk	RSK1 (reversed), RSK2, RSK3 (mean), per scenario (×4)	Likert 1–7	Primary DV (H2), within-subjects
Responsibility attribution	RES1–RES4, per scenario (×4)	Likert 1–7	Secondary DV (H3), within-subjects
Responsibility principles	RES5, RES6, per scenario (×4)	Likert 1–7	Secondary DV
Global preference	P1	7 response options (6 analysis categories)	Secondary DV
General acceptability	P3	Likert 1–7	Secondary DV
AI familiarity	B1	Likert 1–7	Moderator (H4)/covariate
General AI attitudes	G1–G4 (G2, G4 reversed)	Likert 1–7	Covariates
Experience and demographics	B2–B5, D1–D7	Mixed	Covariates/sample description
Manipulation check (perceived AI control)	MAN1, per scenario (×4)	Likert 1–7	Design validation
Scenario difficulty	DIF1, per scenario (×4)	Likert 1–7	Control covariate (fatigue)
Data quality	ATT1, ATT2, CC_A–CC_D	Categorical	Exclusion criteria

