H4. moderation by AI familiarity (partially exploratory)	RM-ANCOVA or linear mixed model with random intercepts: scenario (within) × B1 (centered), sequence between	F (or likelihood-ratio test), *p*, *f*^2^; simple slopes with 95% CI
Global preference (P1)	Goodness-of-fit chi-square over 6 analysis categories (2 undecided options pooled); standardized residuals; consistency with maximum-acceptability scenario, descriptive	χ^2^, *df*, *p*, *w*; standardized residuals
Predictors of acceptability	Person-level multiple regression: mean acceptability on familiarity, general attitudes, demographics	*B*, *SE*, β, 95% CI, R^2^, VIF
P2, P4a/P4b (exploratory)	Brief thematic analysis (P2); descriptive statistics, within-person P4a–P4b difference, and correlations with RES5/RES6	Theme frequencies; Pearson/Spearman *r*
Order dependence (design validation)	Scenario × sequence interaction in the mixed RM-ANOVA; position-adjusted linear mixed model (autonomy + serial position, random intercepts)	*F*, corrected *df*, *p*, partial η^2^ (90% CI); adjusted vs. unadjusted scenario means
Functional form of the autonomy effect	Orthogonal polynomial contrasts (linear, quadratic, cubic); Holm-corrected adjacent-pair contrasts	*F*, *p*, partial η^2^ per contrast; share of the omnibus effect
Autonomy vs. technical complexity	Mixed RM-ANOVA on MAN2 (sequence between); primary models re-estimated with MAN2 as a time-varying covariate	*F*, corrected *df*, *p*, partial η^2^; adjusted scenario means
Between-person heterogeneity (exploratory)	Random-slope linear mixed model; latent-class growth analysis of individual trajectories	Likelihood-ratio χ^2^, *p*; random-slope SD; class sizes, BIC, entropy

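### Objective (iv) asks which implementation model is preferred, but the only inferential analysis of P1 compares each category with a fixed expected share and never one scenario with another.

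*Protocol article*

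**What the plan says.** Section 1.6 lists as secondary objective (iv) "to identify the preferred model of AI implementation in facial reconstructive surgery", in the singular. Table 4 gives P1 as a secondary dependent variable with "7 response options (6 analysis categories").

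Section 2.9.2(vi) plans for P1 "a goodness-of-fit chi-square with standardized residuals over six analysis categories on 5 degrees of freedom". The six categories are the four scenarios, no AI involvement, and one category that pools the two undecided options. The only other use of P1 there is descriptive: "Consistency between stated preference and each participant’s maximum-acceptability scenario is reported descriptively". Table 5 repeats this: "Goodness-of-fit chi-square over 6 analysis categories (2 undecided options pooled); standardized residuals; consistency with maximum-acceptability scenario, descriptive".

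Section 2.5 and Table 2 give a minimum detectable w of 0.21 on 5 degrees of freedom for this test at N = 300. The general settings are "All tests are two-tailed at α = 0.05" and power 0.80. The null proportions are not stated. The Holm-corrected scenario-pair tests of Section 2.9.1 concern the rating composites, not P1.

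**The concern.** Identifying a preferred model means ranking scenarios, so the leading scenario has to be compared with its nearest rival. A goodness-of-fit test does not do this. It asks whether the vector of shares departs from a fixed reference, and its residuals ask the same question one category at a time. A scenario can stand far above its expected share and still be level with another scenario.

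The protocol's own expectations make this pattern plausible. Section 3 expects the largest drop in acceptability at Scenario D, and Section 2.9.2(vi) expects each undecided option to be sparse. If those categories draw few choices, the remaining scenarios rise above the expected share together. Section 2.2 adds that the decision clauses of Scenarios B and C work in the same way, so close shares among the leaders cannot be ruled out.

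At stake is the answer to objective (iv). The planned output could show an overwhelming test result and several large positive residuals, and still hold no inference on which scenario leads.

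**Working it through.** **Inputs from the protocol.** N = 300, six categories, 5 degrees of freedom, α = 0.05, power 0.80. **Assumptions.** Null share 1/6 each, so the expected count is 300/6 = 50. True shares are not given in the protocol and are varied below.

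**1. The plan's own figure.** Solve P(χ²₅ with noncentrality 300·w² > 11.07) = 0.80. This gives w = 0.207, which rounds to the stated 0.21; power at w = 0.21 is 0.814. The figure is right. It measures sensitivity to any departure from the null, not to a difference between two scenarios.

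**2. When a scenario is flagged.** Adjusted residual = (O − 50)/√(50 × 5/6) = (O − 50)/6.455. It exceeds 1.96 when O > 50 + 1.96 × 6.455 = 62.65, that is, from 63 choices (21%). The unadjusted form, (O − 50)/√50, gives 64. Up to four categories can pass 21% at once.

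**3. One example.** Counts A 90, B 84, C 66, D 15, no AI 24, undecided 21 (sum 300).
- χ² = (40² + 34² + 16² + 35² + 26² + 29²)/50 = 5754/50 = 115.1.
- Adjusted residuals for A, B and C are +6.2, +5.3 and +2.5, so three scenarios are flagged.
- Exact binomial test of A against B, 90 of 174: p = 0.70.

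**4. Simulation.** 200,000 multinomial samples of N = 300 per row. Shares are in percent, in the order A/B/C/D/no AI/undecided. The chi-square rejects in about 100% of samples in every row.

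| Assumed shares | At least 2 scenarios flagged | True favourite strictly first (ties counted as success) |
|---|---|---|
| 29/28/27/4/6/6 | 100% | 46% (49%) |
| 27/25/25/8/8/7 | 99.96% | 52% (55%) |
| 31/30/15/6/9/9 | 100% | 57% (60%) |
| 30/28/22/5/8/7 | 100% | 66% (68%) |
| 30/27/18/8/9/8 | 99% | 74% (77%) |
| 35/25/20/5/8/7 | 98% | 98.6% (99%) |
| 45/20/15/5/8/7 | 36% | 100% |

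**5. What a direct contrast can resolve.** Let two leading scenarios hold a joint share s, with true gap d. Power is about Φ[(d√300 − 1.96√s)/√(s − d²)]. With s = 0.60 and d = 0.12: (2.078 − 1.518)/0.765 = 0.73, so power is 0.77. For s from 0.50 to 0.60, power is 0.61 to 0.69 at 10 points and 0.20 to 0.23 at 5 points. About 12 to 13 points are needed for 80%.

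**6. How often a single model would be named** by a two-sided exact test of the most chosen scenario against the next: about 9% of studies at 30/27/18/8/9/8, and about 57% at 35/25/20/5/8/7. With A, B and C all at 25% (D 9, no AI 8, undecided 8) it names one in about 1%, so picking the pair after seeing the counts does not inflate the error in that case.

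**7. The unstated null.** If the reference were 1/7 per single option and 2/7 for the pooled one, the lack of a scenario contrast would be the same. The choice still matters for the chi-square itself. Uniform choice over the seven options gives w = √{6 × [5(1/7 − 1/6)² + (2/7 − 1/6)²]} = 0.32 against one sixth and would be rejected in about 99% of samples.

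**The case against.** The strongest reply is that the protocol contains no rule naming the modal scenario as the winner. Objective (iv) carries no hypothesis, P1 is secondary, and Section 2.12 keeps confirmatory status for H1–H3 and the manipulation and order checks. On that view, reporting the distribution of choices is enough. It is true that no such rule is written, so a reader who infers that the study will declare the mode the preferred model goes beyond the text. What remains is that the objective is worded as identifying one model and the only inference fixed for it cannot do so. P1 is not on the exploratory list in Section 2.12 either.

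A second reply is that Section 2.9.1 plans all six pairwise contrasts on acceptability, with equivalence tests for null pairs. These are useful indirect evidence, but they concern ratings. Stated preference is a separate variable, linked to them only descriptively.

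A third reply is that a statistical analysis plan is to be deposited and may add follow-up contrasts. It is not at hand. The article, however, already fixes the test, categories, degrees of freedom, detectable effect and reported coefficients, so the point concerns what is fixed rather than missing detail.

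The size also depends on chosen shares. With a lead of 10 points or more the mode is almost always right, and with 45% against 20% two scenarios are flagged in only about a third of samples.

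A reader might also carry the problem over to the statements in Sections 3 and 5 on which configurations the public would accept as a starting point. The documents do not support that link: those statements are in the plural, concern acceptability, and do not mention P1.

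**Conclusion.** The point holds as a mismatch between objective (iv) and its planned inference. The chi-square and its residuals cannot rank one scenario above another, whatever the null shares. The stated w = 0.21 is correct and is not in question.

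The practical size is conditional. At N = 300, with leaders within about 1 to 3 points, the most chosen scenario is the true favourite in roughly half to three quarters of studies (46% to 77% across the shares tried and both ways of counting ties), while the chi-square rejects practically always. With a 10-point lead the figure is about 99%. These results rest on assumed shares and, for the flags, on a null of one sixth. It would be too strong to say that several scenarios will be flagged in any event, or that the named preference will be a coin toss: both depend on close leaders and unpopular alternatives.

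The change is worth making before pre-registration. It affects the analysis only.

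**What to change.** In Section 2.9.2(vi) and Table 5:

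- State the null shares and keep the chi-square with residuals as a description of non-uniformity.
- Report the P1 shares with simultaneous 95% confidence intervals.
- Base objective (iv) on a two-sided exact binomial test of the most chosen scenario against the next most chosen scenario, among respondents who chose either. Name a single preferred model only if this test rejects; otherwise report the set of scenarios not distinguishable from the leader.
- Always show the share choosing no AI involvement beside the leading scenario, and do not call a scenario preferred overall if no AI involvement is chosen as often or more often.

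The cost is a few sentences and little code, with no change to items, data or sample size. The real downside is that a single model will often go unnamed: one is named in about 9% of studies at 30% against 27%, and about 57% at 35% against 25%. In the second case the mode would have been right in about 99%, so the rule is cautious there.
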